### Statistical considerations

Data regarding patients’ details, type of surgical procedure and outcomes are entered prospectively into a dedicated database by one of the investigators. Missing or aberrant data will be verified. The rate of neurological events over time will be studied by the classical technique of the time series: this rate will be thus estimated at three sequential time points by MR imaging scan (at baseline, 3 days after surgery and 6 months after surgery). *P* values will be obtained by the two-sided exact method, at the conventional 5% significance level. Data will be analyzed using R 3.3.1 (R Foundation for Statistical Computing, Vienna, Austria: http://www.r-project.org/).

The association between the occurrence of neurological events and the categorical variables will be analyzed by the Fisher’s exact test, describing the outcome as relative frequencies. The relationship between the occurrence of neurological events and the continuous variables will be estimated using the Mann-Whitney test; these results will be expressed as the median (interquartile range (IQR)). The odds ratio of the occurrence of neurological events (categorical dependent variable: major, minor and silent) will be investigated by a complete series of univariate/multivariate binary logistic regression models, performed for the abovementioned covariates (categorical and continuous independent variables).

According to the medical literature, the incidence of MR imaging events in patients undergoing MV surgery through the standard sternotomy approach has been reported to range from 29% to 45% [15, 16]. Assuming the lower value (only MV procedures and patients without vascular disease enrolled in the present study) a total of 706 patients (353 patients per group) would have an 80% chance of demonstrating equivalence between the EAC and theTTC, with a margin of 10% and a 95% confidence. With an expected loss to MR imaging control of 5% (definitive pacemaker implantation, etc.) the total required sample size is estimated to be 741.

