Conversely, more recent experiences show that MIMVS is safe and effective also in the EAC setting. A study performed in our department on 460 consecutive patients who underwent MIMVS through three different approaches—RAP with the EAC (247, 53.7%) or with the TTC (150, 32.6%), and direct cannulation of the ascending aorta with the EAC (ED) (63, 13.7%)—showed that with a correct preoperative assessment and allocation to the most appropriate setting, the rate of early mortality and stroke is low and comparable between the different strategies: overall, no cases of aortic dissection were reported; no differences in terms of stroke rate (1.7% in the EAC group, 2% in the TTC group and no cases in the ED group, *P* = NS) and 30-day mortality (2.1% in the EAC group, 2.7% in the TTC group and 1.6% in the ED group, *P =* NS) were reported. A logistic regression model showed no influences of arterial perfusion and aortic clamping techniques on 30-day mortality and stroke [14]. A trans-European multicentre study on MIMVS in the EAC setting carried out by Casselman et al. supported this suggestion with a stroke rate of 0.8% (4 out of 500 patients) and no aortic dissections [2]. This improvement in the rate of neurological and vascular complications can be explained bearing in mind that these studies have been reported by surgeons with a well-established learning curve and with a consolidated program of patient selection based upon anatomy and clinical history. Another potential influencing factor in the different rates of complication is the type of endoaortic balloon used: while most of the first reports on MIMVS with the EAC used the Endoclamp, most recent series use a mixture of Endoclamp and IntraClude devices. The IntraClude has some different features to enhance manipulation, particularly it has a precurved zone in order to facilitate passage through the aortic arch.

However, to the investigators’ knowledge, the ongoing trial is the first randomized blinded study on neurological outcomes in MIMVS that compares, through MR imaging images, two different clamping techniques.

The study started recruitment in June 2014. With first results expected in December 2016, the findings will be of help in confirming the efficacy and safety of MIMVS.

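### Multivariable logistic regression is planned for major neurological events as for the other categories, but the article's own stroke rates project only about 13 such events, too few for ordinary maximum-likelihood models

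*Protocol article*

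**What the plan says.** The Statistical considerations section of the protocol article describes the outcome of the regression analysis and its method together: "categorical dependent variable: major, minor and silent) will be investigated by a complete series of univariate/multivariate binary logistic regression models". The models are "performed for the abovementioned covariates (categorical and continuous independent variables"). The covariates are neither named nor counted, and nothing separates a frequent outcome from a rare one. The same section plans Fisher's exact test for categorical variables and exact two-sided P values.

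The sample size rests on MR imaging events alone, at an assumed 29%: "a total of 706 patients (353 patients per group) would have an 80% chance of demonstrating equivalence", "with a margin of 10% and a 95% confidence". After allowing for 5% without a postoperative scan, "the total required sample size is estimated to be 741".

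No expected number of major events is stated. The Discussion does report the department's own earlier series by technique: "no differences in terms of stroke rate (1.7% in the EAC group, 2% in the TTC group and no cases in the ED group". It also quotes 0.8% (4 of 500) from a multicentre series with the endoaortic clamp.

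**The concern.** The trial is sized for an outcome expected in nearly a third of patients, yet the same multivariable method is prescribed for an outcome expected in about 2%. With so few events, maximum-likelihood logistic regression can meet separation: some covariate pattern contains no events, and the odds ratio runs to zero or infinity. When the fit does converge, the clamp odds ratio is very imprecise.

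Major events come first in the stated purpose of the study, and the authors expect to show equivalence in neurological events. The Discussion already cites a logistic model from the department's earlier series, in which clamping technique had no influence on stroke, among the evidence for safety. At the quoted rates that series had about 7 strokes among its 397 retrograde-perfusion patients (about 4 of 247 and 3 of 150). A null odds ratio from about 13 events could be read in the same way, although it would be compatible with large differences in either direction.

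**Working it through.** **1. The plan's own sample size.** Equivalence of two proportions by two one-sided tests, with p = 0.29 in both arms, margin 0.10, one-sided 5% per test and 80% power:

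n = 2p(1-p)(z0.95 + z0.90)² / margin² = 2 × 0.29 × 0.71 × (1.645 + 1.282)² / 0.01 = 352.7, so 353 per group and 706 in total. Then 706 × 1.05 = 741.3, the stated 741. The figures reproduce and involve only MR events.

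**2. Expected events.**

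| Outcome | Source of rate | Calculation | Events |
|---|---|---|---|
| MR event | 29%, Statistical considerations | 706 × 0.29 | about 205 |
| Major (as stroke), 706 patients | 1.7% and 2%, Discussion | 353 × 0.017 + 353 × 0.02 = 6.0 + 7.1 | 13.1 |
| Major (as stroke), 741 patients | same | 370.5 × 0.017 + 370.5 × 0.02 | 13.7 |
| Major (as stroke), lower rate | 0.8%, Discussion | 706 × 0.008 to 741 × 0.008 | 5.6 to 5.9 |

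The 95% Poisson range around 13.1 is about 7 to 21. The trial excludes peripheral vascular disease, atrial fibrillation and previous stroke or TIA, so 13 is more likely too high than too low.

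**3. Events per covariate.** With 13.1 events: 4.4 for 3 covariates, 2.6 for 5, 1.6 for 8 and 1.3 for 10.

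**4. Does the model have a finite solution?** Trials of 706 patients were simulated at a 1.85% event rate (the mean of 1.7% and 2%), with the clamp term plus 2 to 12 covariates, half binary and half continuous, none with a true effect. The share with separation or non-convergence was:

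- binary covariates at 30% prevalence: about 2-11%;
- binary covariates at 15% prevalence: about 13-51%.

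Firth-penalised fits never failed. A separate simulation with real covariate effects and mixed prevalences (5% to 50%) failed in about 2% of trials with 3 or 5 terms including the clamp, 13% with 8 and 44% with 10. At the 0.8% rate the same four settings failed in 22%, 29%, 53% and 84%.

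**5. Precision where the fit converges.** In the mixed-prevalence simulation the ratio of upper to lower 95% limit for the clamp odds ratio was about 10 at every model size (about 30 at the 0.8% rate). A hand check without covariates, taking 6 and 7 events in 353 per arm:

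- OR = (6 × 346) / (7 × 347) = 0.85
- SE(log OR) = √(1/6 + 1/347 + 1/7 + 1/346) = 0.56
- 95% CI about 0.28 to 2.57; limit ratio exp(2 × 1.96 × 0.5615) = 9.0

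So almost all of the width is already there in the crude two-by-two table. It reflects the number of events and not the covariates.

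**The case against.** **The sentence can be read another way.** A three-level variable is not binary, and the two preceding sentences treat the occurrence of neurological events as a single outcome. If one any-event model is meant, at least about 205 events support it and the problem disappears. This stands as a caveat. One model per category is the more natural reading of a series of binary models with three named outcomes, but the article does not settle it.

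**The failure rate depends on guesses.** This also stands. A reader might infer that the models will often fail to converge. The article gives neither the number nor the prevalence of covariates, and with common covariates failure is infrequent. The supportable statement is that they may fail, especially with uncommon covariates, many covariates or fewer events.

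**False predictors.** A reader might infer that sparse events make the model pick out noise covariates. They do not. Simulated rates of at least one P < 0.05 among 4, 8 and 12 null covariates were 13%, 28% and 39%, below the ordinary multiplicity figures 1 - 0.95^k of 19%, 34% and 46%. With about 205 events the rates were 18%, 35% and 47%. This is no part of the point.

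**Imprecision is not the model's fault.** Correct, as step 5 of the working shows. It limits what any major-event result can say, and changing the model will not cure it.

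**This belongs in the SAP, and the consequence is small.** Covariate lists and selection rules may well be there. But the article states a method for major events; it does not merely leave one open. The consequence is limited: the primary endpoint is MR events, major events are not among the listed secondary endpoints, and the planned Fisher test remains valid with 13 events.

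**Conclusion.** The point holds in a limited form. As written, the plan commits to multivariable binary logistic models for an outcome projected at about 13 events (about 6 at the lower quoted rate), with no provision for sparseness. Such models may have no finite solution, at a frequency that depends on unstated covariates. Where they do fit, a clamp odds ratio with a roughly 10-fold-wide interval cannot support comparability.

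This rests on three assumptions: major means stroke, one model is fitted per category, and the covariate numbers and prevalences lie in the simulated range. A reader might go further and infer that the trial's main conclusion is at risk. The documents do not support that: the primary MR comparison has its own sample size, which reproduces, and does not depend on these models. The severity is minor to moderate, and the change is a cheap improvement.

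**What to change.** In Statistical considerations:

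- State whether one model is fitted per event category or one for any event, and define a major event.
- Keep the univariate and multivariable logistic series for the MR (any-lesion) outcome.
- For major events, report counts by arm and the EAC minus TTC risk difference with an exact 95% CI, alongside the Fisher test already planned.
- If a model for major events is wanted, use Firth-penalised or exact logistic regression with the clamp and very few prespecified covariates.
- Label the major-event result descriptive, and say that a non-significant difference will not be taken as evidence of comparability.

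The cost is a few sentences and an R package; no extra patients or data are needed. The trial gives up a full multivariable risk-factor model for major events, which about 13 events could not support.

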### Randomization

Patients enrolled in the study are allocated to one of the two parallel treatment groups by equal randomization (Fig. 1). Randomization is conducted using an online computerized service (Sealed Envelope, London, UK). Randomization is handled by an independent statistician who is not involved in trial data collection and analysis. The surgeon is informed about the type of aortic clamping used on the day of the operation; this is facilitated using opaque envelopes containing the patient’s group which the primary investigator has received from the statistician. The primary investigator places this envelope inside the patient’s medical records just before the patient is taken to the operating room, and the surgeon opens the envelope in the operating room.

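### 706 patients give 80% power for equivalence only under two one-sided 5% tests (90% interval); if the stated 95% confidence is applied as a two-sided 95% interval, power is about 67%

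*Protocol article*

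**What the plan says.** The relevant text is in the protocol article under Statistical considerations. The rate of MR imaging events after sternotomy mitral surgery "has been reported to range from 29% to 45% [15, 16]. Assuming the lower value", so the calculation uses 29%. On that basis 706 patients, 353 per group, "would have an 80% chance of demonstrating equivalence between the EAC and theTTC, with a margin of 10% and a 95% confidence". The total is then raised for missing scans: "With an expected loss to MR imaging control of 5% (definitive pacemaker implantation, etc.) the total required sample size is estimated to be 741".

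Earlier in the same section, on significance testing generally, *P* "values will be obtained by the two-sided exact method, at the conventional 5% significance level". Under Randomization, patients are "allocated to one of the two parallel treatment groups by equal randomization".

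The article does not mention a 90% interval or two one-sided tests, and it states no other rule for declaring equivalence.

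**The concern.** An equivalence sample size depends on the level of the interval that must fit inside the margin. Two one-sided tests at 5% each match a two-sided 90% interval; a two-sided 95% interval corresponds to 2.5% per side and needs more patients for the same power. The article gives 95% as its confidence, but its number of patients is the one for 5% per side.

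The comparison affected is the main one. The primary endpoint is the difference in MR imaging events between the two clamps, and the Discussion section of the abstract says that equivalence is expected. An analyst working from the article alone would probably build a 95% interval. Two truly equivalent techniques would then fail to show equivalence about one time in three, not one time in five. If the level is still open when results are seen, it could also be chosen according to which interval happens to fit.

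**Working it through.** **Inputs, all from Statistical considerations**
- Event rate p = 0.29, taken as equal in both arms (true difference zero).
- Margin m = 0.10. It is read as absolute percentage points, and this reading reproduces the stated figure.
- Power 80%, so β = 0.20. For equivalence with no true difference, β is split between the two sides, giving z(0.90) = 1.2816.
- 353 per group, 706 in total; 5% loss to imaging; stated total 741.

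**Step 1: reproduce the stated size**

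n per arm = 2p(1 − p)(z₁₋ₐ + z₀.₉₀)² / m², where a is the error rate per side and 2p(1 − p) = 2 × 0.29 × 0.71 = 0.4118.

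- a = 0.05 (90% interval): 0.4118 × (1.6449 + 1.2816)² / 0.01 = 352.66, so 353 per arm and **706** in total. This is an exact match.
- a = 0.025 (95% interval): 0.4118 × (1.9600 + 1.2816)² / 0.01 = 432.7, so 433 per arm and **866** in total.

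**Step 2: rule out other origins of 706**
- One-sided non-inferiority at 80% power gives 510 in total at 5% and 648 at 2.5%.
- A superiority comparison of 29% with 39% at two-sided 5% gives 352 per arm. That is close but not equal, and the text says equivalence.

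The equivalence formula at 5% per side is the only one of these that returns 353.

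**Step 3: power at 353 per arm**

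SE = √(0.4118 / 353) = 0.03415, so m/SE = 2.928.

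Power = 2Φ(m/SE − z₁₋ₐ) − 1.

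| Rule | Normal approximation | Exact binomial enumeration, Wald interval |
|---|---|---|
| 5% per side, 90% interval | 2Φ(1.283) − 1 = 80.0% | 80.2% |
| 2.5% per side, 95% interval | 2Φ(0.968) − 1 = 66.7% | 66.7% |

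If all 741 patients were evaluable (370.5 per arm), power with a 95% interval would be about 70%. The allowance for loss therefore does not close the gap.

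**Step 4: the loss adjustment**
- 706 × 1.05 = 741.3, which is how 741 arises.
- Keeping 706 evaluable after a 5% loss needs 706 / 0.95 = 743.2, or 744 as an even total (372 per group).
- 741 × 0.95 = 704 evaluable, 352 per arm. Under the 5%-per-side rule, m/SE = 2.924 and power = 2Φ(1.279) − 1 = 79.9%.

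**The case against.** The best defence is that 706 is not a miscalculation. Two one-sided tests at 5% each form a standard 5%-level equivalence test. The article speaks of 95% confidence and does not use the word interval, so the phrase may be a loose label for one minus a 5% error rate. The exact match to 353 supports this. On that reading the confidence, the power and the sample size agree, and only the wording needs attention. This stands, and it is why the 67% is conditional on how the phrase is applied.

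A reader might also take the two-sided 5% sentence as proof that a 95% interval is meant. The article does not support that. The sentence is about P values in general, and the tests described after it are Fisher's exact test, Mann-Whitney and logistic regression. None of these sets the equivalence interval.

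It can further be said that the interval level is often left to the analysis plan. That would answer a complaint that the level was missing. Here a level is stated, and on its ordinary reading it does not deliver the stated power. Nothing else in the article corrects that reading.

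On the loss adjustment, the objection that it is trivial is right: three patients and about 0.1 percentage point of power. Nor does the odd total of 741 conflict with equal randomization, which does not require an even number.

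**Conclusion.** The point holds in conditional form. With 29% in both arms and a 10-point margin, 353 per group gives 80% power for two one-sided 5% tests and about 67% if equivalence is judged by a two-sided 95% interval. As worded, the article points the reader to the second rule while its sample size comes from the first.

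A reader might go further and conclude that the trial is underpowered, or that it must recruit 866 evaluable patients. The article does not support either conclusion, because it never commits to a two-sided 95% interval and the number fits a legitimate 5%-level test exactly.

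The figures assume equal true rates of 29%. At 45%, the upper end of the article's cited range, the two powers at 353 per arm would be 69.5% and 52.3%, so the gap between the rules does not depend on using the lower rate. The loss-adjustment slip is real but negligible.

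**What to change.** Before any unblinded analysis, adopt one of the following and state it.

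- **(a)** Equivalence is tested by two one-sided tests at 5% each and is declared if the two-sided 90% confidence interval for the difference in MR imaging event rates lies within ±10 percentage points; 353 evaluable patients per group give 80% power. The 95% interval is also reported.
- **(b)** Equivalence is declared if the two-sided 95% confidence interval lies within ±10 percentage points; 706 evaluable patients give about 67% power.

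In the same edit, either change the loss-adjusted total to 744 (372 per group), or keep 741 and say that it leaves about 704 evaluable, with power of about 79.9% under (a).

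The article expected first results in December 2016 and also says that recruitment continues, so it does not show whether results by arm have been seen. If they have, the restatement should say so and both intervals should be reported.

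The cost is rewording only. Under (a) the stated confidence level becomes less favourable, and under (b) the stated power does. Neither option needs more evaluable patients than the 706 planned; choosing 744 would add three to the recruitment total.

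### The 80% power of 353 patients per group holds for two one-sided 5% tests (a 90% interval); if the stated 95% confidence means a two-sided 95% interval, as it ordinarily would, the power is about 67%

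*Protocol article*

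**What the plan says.** The sample-size paragraph of the protocol article (Statistical considerations) starts from published rates of MR imaging events after mitral surgery through sternotomy. That incidence "has been reported to range from 29% to 45% [15, 16]. Assuming the lower value", so 29% is the planning rate. From this it derives "a total of 706 patients (353 patients per group"), who "would have an 80% chance of demonstrating equivalence between the EAC and theTTC, with a margin of 10% and a 95% confidence". The Randomization section confirms equal allocation.

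Two paragraphs earlier, the same section says that P "values will be obtained by the two-sided exact method, at the conventional 5% significance level". This is the only significance level given in the article. Neither a 90% interval nor a pair of one-sided tests is mentioned.

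**The concern.** An equivalence claim rests on an interval for the difference lying wholly inside the margin. The confidence level of that interval fixes both the power and the largest observed difference that still counts as equivalent. Two one-sided tests at 5% each correspond to a 90% interval; a 95% interval corresponds to 2.5% on each side and is harder to satisfy with the same number of patients.

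The sentence attaches 95% confidence to the 80% power. An analyst who takes it at face value will construct a 95% interval, and the sample size was not calculated for that.

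Two things are at stake. One is the advertised chance of success when the two clamps are truly the same. The other is the decision rule: some observed differences pass under one reading and fail under the other. The article's Discussion expects to show equivalence, so this rule bears directly on the trial's main conclusion.

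**Working it through.** **Inputs, all from the protocol article**

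- Event rate p = 0.29 in both groups (Statistical considerations). The true difference is taken as 0; this is an assumption, and it is the one that reproduces the plan's figure.
- Margin d = 0.10, read as an absolute difference (same section).
- Power 80%, with 353 evaluable patients per group (same section).
- Allocation 1:1 (Randomization).

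**Step 1. Reproduce the plan's figure.** For equivalence of two proportions with no true difference, the 20% type II error is split over the two sides, so the power quantile is z(0.90) = 1.282:

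n per group = 2p(1 − p) × (z(1 − a) + 1.282)² / d², where a is the error rate on each side and 2p(1 − p) = 2 × 0.29 × 0.71 = 0.4118.

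| Error per side | Matching interval | z(1 − a) | n per group | Total |
|---|---|---|---|---|
| 5% | 90% | 1.645 | 352.7, so 353 | 706 |
| 2.5% | 95% | 1.960 | 432.7, so 433 | 866 |

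The first row is the plan's number exactly. A one-sided non-inferiority calculation at 80% power does not give it: that needs 255 per group at 5% one-sided and 324 at 2.5%. Pooled and unpooled variances coincide because the two rates are equal.

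**Step 2. Power of 353 per group under each reading.**

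SE = √(0.4118 / 353) = 0.03416, so d / SE = 2.928.

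Power = 2Φ(d / SE − z(1 − a)) − 1.

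- 90% interval: 2Φ(2.928 − 1.645) − 1 = 2Φ(1.283) − 1 = 80.0%.
- 95% interval: 2Φ(2.928 − 1.960) − 1 = 2Φ(0.968) − 1 = 66.7%.

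**Step 3. Check without the normal approximation to power.** Enumerating every pair of binomial counts at 29% v 29%, with 353 per group:

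| Deciding interval | Wald | Newcombe |
|---|---|---|
| 90% | 80.2% | 80.4% |
| 95% | 66.7% | 67.2% |

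**Step 4. What changes in the decision.** With the planning SE, the largest observed difference still declared equivalent is d − z(1 − a) × SE:

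- 90% interval: 0.10 − 1.645 × 0.03416 = 4.4 points.
- 95% interval: 0.10 − 1.960 × 0.03416 = 3.3 points.

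Observed differences between about 3.3 and 4.4 points therefore pass under one reading and fail under the other. The chance of declaring equivalence when the true rates are 29% and 39%, at the edge of the margin, is about 5% with the 90% interval and 2.5% with the 95% interval.

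**The case against.** The strongest defence is that 95% confidence here means one minus alpha, with alpha at 5% for each one-sided test. On that reading the event rate, margin, power and group size all agree. The exact match in Step 1 also makes it likely that the calculation was done this way. Two one-sided tests at 5% each are a standard equivalence design. This defence stands as far as the number goes: 706 is sound for that design. It does not rescue the wording, because the article does not say that this is what the phrase means, and most readers will take it as a two-sided 95% interval.

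Several stronger readings are tempting, and the article does not support them.

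- A reader might infer that the article commits the trial to a 95% confidence interval. It names no interval; it says only "with a margin of 10% and a 95% confidence".
- A reader might infer that the stated size, power and confidence level cannot all be true together. They conflict only on the two-sided-interval reading.
- A reader might use the two-sided 5% level as proof of the 95% reading. That sentence concerns P values, follows the text on event rates over time and precedes the association tests and regression models. Two-sided 5% tests of association can coexist with an equivalence test at 5% per side.
- A reader might infer that the interval will be chosen once the results are known. Nothing in the article suggests this.

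It can also be said that the deciding interval is a detail for the analysis plan, which is not shown. That would answer a complaint about missing detail. The point here is about a phrase the article does contain, attached to a power figure that does not hold under the phrase's usual meaning.

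**Conclusion.** The point holds as a fault in how the power statement is worded, not as an error in the sample size. With 353 evaluable patients per group, power is 80% if equivalence is judged by a 90% interval and about 67% if it is judged by a 95% interval. On the second reading, the chance of failing to show equivalence between truly identical clamps is about 33%, not 20%. That larger risk is conditional on a 95% interval being used to decide.

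The figures assume a 29% event rate in both groups, no true difference, an absolute margin of 10 points and 353 evaluable patients in each group.

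**What to change.** Amend one sentence before any comparison by arm, in one of two ways, and carry the same wording into the statistical analysis plan.

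- **(a)** Replace the 95% confidence phrase with: *two one-sided 5% tests, i.e. the 90% confidence interval of the risk difference within ±10 percentage points*. The 353 per group and the 80% power then stand. The cost is a stated confidence level that looks less demanding.
- **(b)** Keep 95%, state that the two-sided 95% confidence interval of the risk difference decides equivalence, and restate the power of 353 per group as about 67%. The cost is a less favourable stated power.

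Neither option asks for more patients; the 433 per group above only shows the size of the gap. Either one settles in advance which interval decides, and so whether observed differences of about 3.3 to 4.4 points count as equivalent.
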